### 2.9. Interventions

#### 2.9.1. Experimental Group

MYN is produced and packed by Sichuan Purity Pharmaceutical Co., Ltd. To ensure the stability of the drug, the same batch of drugs will be used in this study (drug batch number: 051–210917). MYN is currently under patent review. We have uploaded all of the specific components, dosage, and other information of MYN to the official website of China National Intellectual Property Administration, which is open for access and can be found on the patent search and service system page of the official website of China National Intellectual Property Administration [28] via publication no.: CN109908209A. MYN will be administered intranasally and two pumps/nostril will be sprayed twice daily. The drug will not be administered once the patient meets the clinical control standard for two weeks. The shortest treatment time will be not less than four weeks, and the longest treatment time will be not more than three months.

#### 2.9.2. Control Group

Mometasone furoate aqueous nasal spray (NASONEX) is produced and packed by Schering-Plow Labo N. V. (drug batch number: H20140100). Mometasone furoate aqueous nasal spray will be administered intranasally, and two pumps/nostril will be sprayed once a day. The drug will not be administered once the patient meets the clinical control standard for two weeks. The shortest treatment time will be not less than four weeks, and the longest treatment time will be not more than three months.

Any other Western or Chinese medicines for AR are prohibited during this trial.

#### 2.9.3. Clinical Control Standard

After the subjects start treatment, the rhinitis control assessment test (RCAT) will be applied every week for each subject. If the RCAT score is >21, AR is well controlled (clinical control standard); if the RCAT ≤21, it is not controlled.

### 2.10. Outcomes

#### 2.10.1. Baseline Assessment

The demographic characteristics of the subjects (gender, age, current residence, education, and occupation) and general clinical data (medical history, previous treatment history, and AR severity grade) will be collected.

#### 2.10.2. Primary Outcomes

The primary outcome is the six-month recurrence rate of AR after intervention withdrawalFollow-up: subjects will enter the follow-up period after withdrawal of medications. Once a relapse occurs, the patient's recurrence time will be recorded, and the follow-up ends. Otherwise, the follow-up will continue until six months after drug withdrawal.Definition of recurrence/relapse: when the RCAT score ≤21 during follow-up, the patient will be considered in a relapse stateDefinition of six-month recurrence rate: six-month recurrence rate = number of recurrent AR patients in six months/total number of patients × 100%The RCAT has sufficient reliability, validity, and responsiveness and is a simple patient self-assessment scale [29]. RCAT can be used to assess a patient's rhinitis control status in clinical practice [30]. During the treatment stage, we will collect the RCAT scale online once a week, and during the follow-up stage, we will collect the RCAT scale online every two weeks.

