**Methods:**

In this study, a multicenter, open-label, randomized, and parallel-arm trial will be conducted at three study centers. A total of 190 subjects aged 18–65 with persistent and moderate-severe AR (Qi deficiency and blood stasis syndrome) will be randomly assigned to receive the modified Yupingfeng nasal spray or mometasone furoate aqueous nasal spray. When subjects' rhinitis control assessment test (RCAT) score is >21 for two weeks, they will stop taking the medication and enter the follow-up. Once a relapse occurs, the time point will be recorded, and the follow-up stops. The primary outcome is the six-month recurrence rate of AR after intervention withdrawal. The secondary outcomes are the one-month recurrence rate of AR, the RCAT score, the duration of follow-up, the duration of medication, the nasal endoscopic results, and questionnaires to evaluate symptoms, signs, and quality of life. The mechanism outcomes include some indicators that may be associated with AR recurrence. In addition, electrocardiograms and other safety indicators will be applied to evaluate the drug's safety. *Discussion*. This is the first study to explore the efficacy of traditional Chinese medicine nasal spray on AR from the perspective of controlling recurrence. The results of this trial may provide valuable clinical evidence for controlling the recurrence of this disease by pharmacotherapy. *Trial Registration*. This study was registered with registration number ChiCTR2100047053 (Chinese Clinical Trial Registry, https://www.chictr.org.cn/showproj.aspx?proj=127432 on June 7, 2021).

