### 2.12. Statistical Methods

All analyses will be based on the intention-to-treat (ITT) principle. Missing data will be reduced to a minimum. For data loss caused by subject drop-out, data from the previous measurement will be carried forward. The frequency, percentages, means and standard deviations, medians, and quartiles will be calculated for descriptive analysis. Intergroup comparisons of continuous variables will be performed using the *t*-test or Mann–Whitney *U* test. Categorical variables will be compared using Pearson *χ*^2^ tests or Fisher exact tests. Time-to-event outcomes will be analyzed using the Kaplan–Meier method and Cox proportional hazard models. Two-tailed *p* < 0.05 will be considered statistically significant for all analyses. All statistical analyses will be conducted using SPSS version 25.0 for Windows (IBM Corporation, Armonk, NY, USA).

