*Note*. w, week; w1, the first week; w2, the second week; Wx, timepoint when subjects meet the clinical control standard; drug withdrawal (wx+2), timepoint when subjects meet the clinical control standard and last for two weeks.

**Table 4 tab4:** Ethical review approvals.

Number	Ethics committees' name	Approval registration number
1	Medical Ethics Committee of the Hospital of Chengdu University of Traditional Chinese Medicine	2021KL-046
2	Ethics Committee on Biomedical Research, West China Hospital of Sichuan University	n/a
3	Medical Ethics Committee of the Sichuan Provincial Hospital of Integrated Traditional Chinese and Western Medicine	KY-HX-2021-039

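### The protocol conflicts on whether a patient still uncontrolled at the three-month treatment limit counts as a relapse or a non-recurrence in the primary outcome, and the choice can reverse the comparison

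*Protocol article*

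**What the plan says.** - **Formula (section 2.10.2).** The six-month recurrence rate is "number of recurrent AR patients in six months/total number of patients". Recurrence is an RCAT score of 21 or below during follow-up; prior control is not mentioned.
- **Entry to follow-up, first version.** In the Abstract (Methods), patients whose "score is >21 for two weeks, they will stop taking the medication and enter the follow-up". The note to Table 3 defines the drug-withdrawal visit (wx+2) as the "timepoint when subjects meet the clinical control standard and last for two weeks".
- **Entry to follow-up, second version.** Section 2.10.2 says "subjects will enter the follow-up period after withdrawal of medications", without requiring control.
- **Treatment limit.** Section 2.9.1 says "the longest treatment time will be not more than three months", and section 2.9.2 sets the same limit for mometasone.
- **Analysis set (section 2.12).** "All analyses will be based on the intention-to-treat (ITT) principle". Carry-forward is specified for drop-out only.
- **Planning rates (section 2.6).** Six-month recurrence of about 50% (MYN) and 75% (mometasone), a 5-point superiority margin, one-sided alpha 2.5%, 86 per group, 190 in total.

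**The concern.** A patient who reaches three months with an RCAT score of 21 or below has not dropped out, so the missing-data rule does not apply, and intention to treat keeps the patient in the denominator. The text supports two opposite scores.

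Under the Abstract and the Table 3 note, the patient never has a withdrawal visit as defined there, never enters follow-up, and so cannot recur. A treatment failure is then counted among the patients without recurrence. Under section 2.10.2 read alone, the same patient stops medication at the limit, enters follow-up, and relapses at the next two-weekly RCAT if the score stays at 21 or below.

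On the first reading the primary rate is the product of reaching control and recurring after control, so a lower control rate lowers the reported recurrence rate. Unequal control is plausible: section 3 describes intranasal corticosteroids as first-line treatment for this population. Subjects and researchers are also unblinded, so the choice should not be left until results by arm can be seen.

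**Working it through.** **1. The plan's own figure.** Superiority by a margin with unpooled variance: n = [0.50×0.50 + 0.75×0.25] × (1.960 + 0.842)² / (0.25 − 0.05)² = 85.85, so 86 per group as stated. 86 × 1.1 is about 95 per arm, or 190 in total.

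**2. Inputs for the check.** 95 per arm (190 at 1:1, sections 2.2 and 2.6). *Assumed:* recurrence among controlled patients, r = 75% in both arms, so there is no true effect on recurrence. *Assumed:* the share reaching control, c, which the protocol does not give for either arm; a range is shown.

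**3. Formulas.**
- Reading A (Abstract, Table 3 note), never-controlled patients as non-events: rate = c × r.
- Reading B (section 2.10.2 alone, if the score stays at 21 or below), never-controlled patients as events: rate = 1 − c × (1 − r).

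**4. Results, MYN versus mometasone.**

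| Control reached | Reading A | Difference for MYN | Reading B | Difference for MYN |
|---|---|---|---|---|
| 85% vs 85% | 63.75% vs 63.75% | 0 | 78.75% vs 78.75% | 0 |
| 75% vs 85% | 56.25% vs 63.75% | 7.5 points better | 81.25% vs 78.75% | 2.5 points worse |
| 60% vs 85% | 45.0% vs 63.75% | 18.75 points better | 85.0% vs 78.75% | 6.25 points worse |

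**5. Probability of falsely declaring MYN superior under reading A** (exact binomial enumeration, 95 per arm, two-sided 5% or the equivalent one-sided 2.5%).

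| Control reached | Pearson chi-square (section 2.12) | Against the 5-point margin (section 2.6, unpooled) |
|---|---|---|
| 75% vs 85% | 18% | 6% |
| 60% vs 85% | 74% | 51% |

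Both tests are shown because section 2.12 lists the chi-square test while section 2.6 plans against the margin.

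**6. Power if never-controlled patients are events.** *Assumed:* 10% never controlled in each arm, and the planned 50% and 75% apply to controlled patients. The rates become 0.10 + 0.90×0.50 = 55% and 0.10 + 0.90×0.75 = 77.5%. By enumeration, power against the margin falls from about 84% (83.5%) to about 74% with 95 per arm, and from about 80% to 70% with 86.

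**The case against.** The strongest reply is that section 2.10.2 is the operative definition and, taken literally, already scores these patients: medication ends at the limit, follow-up begins, and a low RCAT is a relapse. The Abstract says what happens when control is reached, not that nothing else can start follow-up. This is right as far as it goes. A reader might infer that the protocol gives never-controlled patients no place at all; section 2.10.2 does not support that. What remains is a conflict. The Table 3 note defines withdrawal only through sustained control, the six-month clock runs from withdrawal, and section 2.13 describes a course from onset to control to recurrence.

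It may also be said that Figure 1, the body of Table 3 or the full protocol shows a path for these patients. They are not available here and may do so, but the passages quoted would still disagree.

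The figures are conditional, and that stands. All the unequal cases assume MYN controls fewer patients, whereas section 1 reports that MYN improves symptoms. A reader might also infer that the planned 50% and 75% necessarily shrink (for example to 40% and 60% with 80% controlled) and power is lost. Section 2.6 does not say these rates are conditional on control; they may already refer to all patients.

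Finally, section 2.1 states the aim as preventing recurrence, and counting non-control as an event widens that. This is a real cost. The alternative of analysing controlled patients only compares groups selected after randomisation and departs from intention to treat.

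**Conclusion.** The concern holds as an inconsistency in the definition of the primary event. One of the two stated pathways, combined with the all-patients denominator, biases the primary result in favour of the arm with worse control; the other does not. Across the assumed control rates, the spurious benefit on the first pathway runs from zero (equal control) through 7.5 points (75% vs 85%) to 18.8 points (60% vs 85%), and the second pathway reverses the sign in both unequal cases. These sizes rest on equal 75% recurrence among controlled patients and on control rates that the protocol does not supply. They show what the ambiguity could do and do not predict this trial's result. The documents do not show that MYN controls fewer patients, nor that the biased reading is the intended one.

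**What to change.** 1. Reconcile the Abstract, section 2.10.2 and the Table 3 note on who enters follow-up and when the six-month clock starts.
2. State that the primary analysis includes all randomised patients, and that those who never reach the control standard by the treatment limit are scored as events, never as non-recurrences.
3. Report the proportion reaching control by arm beside the primary result.
4. Give recurrence among controlled patients only as a supportive, non-randomised comparison.
5. State whether the 50% and 75% in section 2.6 refer to this denominator, and restate the power if they do not.

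The cost is wording, settled before any comparison by arm; the weekly RCAT already records control, so no new data are needed. The drawbacks are that the outcome then covers failure to reach control as well as recurrence, and that power may fall below the planned 80%: to about 74% against the margin with 95 per arm under the 10% assumption in step 6 of the working.

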#### 2.10.3. Secondary Outcomes

The secondary outcomes are the one-month recurrence rate of AR, the RCAT score, the duration of follow-up (days), the duration of medication (days), the nasal endoscopic results, the visual analog scale (VAS), the total nasal symptom score (TNSS), the rhinoconjunctivitis quality of life questionnaire (RQLQ), the total ocular symptom score (TOSS), the TCM syndrome score of spleen Qi deficiency and lung Qi deficiency, and the classification and determination scale of constitution of TCM.(1)$$\begin{array}{c} \text{Definition of one}-\text{month recurrence rate}=\frac{\text{Number of recurrent AR patients in one month}}{\text{Total number of patients}}\times 100\%. \end{array}$$

All of these will be recorded before/after the intervention and when relapse occurs on the paper version of the CRF.

#### 2.10.4. Mechanism Outcomes

Serum: endogenous carbon monoxide in serum will be measured by colorimetry. PAF will be measured by quantitative real-time PCR (qRT-PCR). The expression levels of TLR4, CD80, CD86, CCR6, and CCR7 on the surface of DCS will be detected by flow cytometry (FCM).Cells: epithelial nasal mucosa cells will be extracted with a nasal brush. The mRNA and protein expression levels of TLR4, MyD88, and TRIF in the nasal mucosa will be measured by qRT-PCR and Western blotting, respectively. The protein expression levels of HO-1 and TLR2 will be measured by Western blot.Nasal lavage fluid: the nasal lavage fluid concentrations of IL4, IFN*γ*, TNF-*α*, NF-*κ*Β, IL-6, and IL-12 will be measured by ELISA.Not all subjects need to participate in the collection of mechanism samples. A subgroup of 18 subjects will be asked to participate in an optional study, in which the epithelial cells of the nasal mucosa will be extracted with a nasal brush, and the serum and nasal lavage fluid will be collected to measure the mechanism indicators. These samples will be collected at baseline and after drug withdrawal. Regardless of treatment allocation, subjects can voluntarily participate in this part of the trial through instructions provided on the informed consent form. To ensure a consistent baseline, we will use a random number table to randomly select nine willing subjects from each of the experimental and control groups.

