### 2.16. Confidentiality

All study-related information (basic information, data, laboratory reports, forms, and informed consent) will be identified by the random sequence number and stored by the PI in lockers or encrypted on designated computers. Serum, nasal lavage fluid, and nasal mucosa samples from this study will be placed in a locked refrigerator. Data containing personal identifiers will be destroyed three years after the end of the trial.

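### Mechanism panel: the assay named for PAF (qRT-PCR) cannot measure it, and the dendritic-cell flow cytometry is listed under serum with no cell-containing blood specimen named

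*Protocol article*

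**What the plan says.** Section 2.10.4 of the protocol article groups the mechanism markers under three sample headings.

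- **Serum.** The group opens with "Serum: endogenous carbon monoxide in serum will be measured by colorimetry". It continues with "PAF will be measured by quantitative real-time PCR (qRT-PCR") and then "The expression levels of TLR4, CD80, CD86, CCR6, and CCR7 on the surface of DCS will be detected by flow cytometry (FCM").
- **Cells.** Brushed nasal epithelial cells are used for TLR4, MyD88 and TRIF, for which the text specifies both mRNA and protein, and for HO-1 and TLR2 protein.
- **Nasal lavage fluid.** Six markers are measured by ELISA, in a list that begins "Nasal lavage fluid: the nasal lavage fluid concentrations of IL4, IFN" and includes NF-κB.

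On collection, the section says that "the epithelial cells of the nasal mucosa will be extracted with a nasal brush" and that "the serum and nasal lavage fluid will be collected to measure the mechanism indicators". Samples are taken at baseline and after drug withdrawal. Participation is limited and voluntary: "A subgroup of 18 subjects will be asked to participate in an optional study", nine from each arm. On storage, section 2.16 says: "Serum, nasal lavage fluid, and nasal mucosa samples from this study will be placed in a locked refrigerator".

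The abbreviation list expands neither PAF nor DCS.

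**The concern.** An endpoint can be derived only if the assay detects the analyte and the specimen contains it. Two items in the serum group appear to fail this test. PAF is paired with a method that detects nucleic acid, and the dendritic-cell surface markers are paired with a fluid that contains no cells.

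Exploring the mechanism of action is a stated aim of the trial (Introduction and section 2.2). The baseline sample is taken before treatment, so a missing or unsuitable specimen cannot be replaced later for that subject. With nine subjects per arm there is little room to lose any. Followed literally, the text would leave the PAF endpoint without a valid value and the dendritic-cell endpoint without cells to analyse.

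**Working it through.** No figure in the plan belongs to this point, so nothing numerical needs reproducing. The check sets each marker, specimen and assay in section 2.10.4 against the samples that the article names.

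**Step 1: count the panel (marker-by-specimen entries).**

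- Serum: carbon monoxide 1 + PAF 1 + TLR4, CD80, CD86, CCR6, CCR7 on dendritic cells 5 = 7.
- Brush cells: TLR4, MyD88, TRIF, HO-1, TLR2 = 5.
- Lavage fluid: IL-4, IFN-γ, TNF-α, NF-κB, IL-6, IL-12 = 6.
- Total: 7 + 5 + 6 = 18 entries. (That this equals the number of subjects is a coincidence.)

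**Step 2: PAF.** Assumption: PAF means platelet-activating factor, the natural reading in an allergy protocol.

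- It is a phospholipid, and no gene transcript encodes it. qRT-PCR quantifies nucleic acid, so it cannot return a PAF level from any specimen.
- It could measure mRNA of a related receptor or enzyme, but the text names none.
- The cells paragraph says mRNA where mRNA is meant (TLR4, MyD88, TRIF). The PAF sentence does not.

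**Step 3: dendritic-cell markers.** Assumption: DCS means dendritic cells.

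- Reading surface expression by flow cytometry needs intact cells. Serum is the cell-free part of clotted blood.
- Three places agree on the specimens: the group heading (serum), the collection sentence in 2.10.4 (brush cells, serum, lavage fluid) and the storage sentence in 2.16 (serum, lavage fluid, nasal mucosa).
- The only cells named are nasal epithelial cells, and they are assigned to PCR and Western blotting.
- Section 2.10.5 plans routine blood tests before and after the interventions, but for safety. No sentence assigns a blood-cell specimen to the flow cytometry.

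**Step 4: the rest of the panel.** The remaining entries are carbon monoxide 1 + brush cells 5 + lavage 6 = 12. None has a mismatch of this kind.

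**Step 5: size.** One entry has an assay that cannot measure the named analyte. Five entries have no suitable named specimen on the text. Together that is 1 + 5 = 6 of 18 entries, confined to 9 + 9 = 18 subjects, or 18/190 = 9.5% of the planned sample.

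**The case against.** The strongest reply concerns the dendritic-cell markers. Serum is a one-word heading in a condensed article. Only the carbon monoxide sentence says that the measurement is made in serum, whereas the flow-cytometry sentence refers to the surface of cells, so cells are plainly intended. Tube type and cell isolation commonly sit in a full protocol or procedure manual. Section 2.17 points to a complete protocol on the registry and section 2.14 to an SOP, and neither is shown. The storage list in 2.16 need not cover blood that is analysed fresh. Much of this stands: the authors may well have meant a blood draw, and nothing shows that a wrong tube was used. What remains is that the article does not merely omit the specimen. It states one that does not fit, and its collection sentence repeats it.

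For PAF, the reply is that neither abbreviation is expanded and that the sentence may be an editing slip. That is why the reading is marked as an assumption. Under the natural reading, however, the stated method is wrong and is not a detail left to another document.

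A reader might also infer that NF-κB by ELISA in lavage fluid is a third error of the same kind, and that the whole group of markers cannot be derived. The documents do not support that. NF-κB is an intracellular transcription factor, so its concentration in lavage fluid may be hard to interpret. But lavage fluid can contain cells or cell contents, an immunoassay can return a value, and the article claims only a concentration. Measuring it in brush cells instead would be a preference.

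**Conclusion.** The point holds in two parts of different strength.

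- **PAF by qRT-PCR** is a wrong stated method, provided that PAF means platelet-activating factor. As written, this endpoint would return no valid PAF level.
- **The five dendritic-cell markers** have no cell-containing blood specimen on the text, provided that DCS means dendritic cells and serum is meant literally. This needs a specimen correction. It does not prove that the markers are unobtainable, because serum may stand for a blood draw.

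NF-κB is not part of the error. The consequence is limited to an optional, exploratory panel. The primary outcome, the secondary outcomes, the sample size and the main analyses do not change. The correction is nevertheless worth making, because it is cheap and a lost baseline sample cannot be recovered.

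**What to change.** In section 2.10.4:

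1. Replace qRT-PCR for PAF with an assay that measures the lipid in serum or plasma, such as an immunoassay or mass spectrometry. If mRNA of a related receptor or enzyme was meant, name the transcript and the cells from which RNA will be taken.
2. Take the dendritic-cell markers out of the serum group, and name an anticoagulated whole-blood or mononuclear-cell specimen for the flow cytometry, drawn at the same venepuncture. Add it to the collection sentence.
3. Expand PAF and DCS.
4. Withdraw either endpoint for subjects whose samples cannot support it, and report how many subjects contribute.

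The cost is a wording change, one extra tube at a blood draw and a different PAF kit for 18 subjects. The main downside is timing. Recruitment began on September 1, 2021, before the article appeared in August 2022, so some substudy subjects may already lack a suitable baseline sample and could not contribute to these endpoints.
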